[figure not shown]

## Summary

Patients with type 2 diabetes mellitus have a high risk for a multitude of severe complications. This epidemiological cohort study aims at examining determinants and predictors of long-term prognosis in about 1,500 patients with type 2 diabetes mellitus, who are recruited and followed up in a general practitioner setting. A randomised controlled trial will be conducted in a subgroup of around 250 patients with poor glycemic control ( $\text{HbA}_{1c} > 7.5\%$ ), in order to investigate whether supportive patient-centred telephone counselling improves the primary outcome  $\text{HbA}_{1c}$  and secondary outcomes (complications, hospital admissions, mortality) above usual care.

## **1. Introduction**

Diabetes mellitus is one of the most prevalent metabolic diseases in Western industrial countries. General practitioners (GPs) are usually the main care takers of diabetes patients (1). The goals of diabetes therapy are based on evidence-based guidelines (2). In Germany, currently around 5 million people (6 % of the general population) have type 2 diabetes and prevalence is expected to increase in the future (3, 4).

The quality of diabetes care determines prognosis in diabetes patients. Especially the willingness of affected patients to engage in an adequate patient self-management is of great importance. Although current epidemiological studies have shown some improvements in diabetes care and therapy at a population level, still a considerable proportion of patients have a poor glycemic control (5). Furthermore, population-based epidemiological longitudinal data on determinants and predictors of long-term prognosis of diabetes patients in Germany are very sparse.

Patient-centred diabetes care that incorporates patients' resources can improve important outcome parameters of diabetes therapy. Successful diabetes management, amongst others, is based on a close collaboration of GP and patient that considers personal coping strategies of the patient, and on a good patient self-management (6, 7). However, only little is known about which factors and structures determine successful patient self-management.

## **2. Objectives of the study/Outcomes**

This epidemiological cohort study aims at examining determinants and predictors of long-term prognosis in patients with type 2 diabetes mellitus in a GP setting. A randomised controlled trial will be conducted in a subgroup of patients with poor glycemic control, in order to investigate whether supportive patient-centred telephone counselling improves the primary outcome HbA1c and secondary outcomes (diabetes-related complications, diabetes-related hospital admissions, mortality) above usual care. The study will also examine how eligible patients unwilling to participate in the intervention study differ from participants with regards to basic characteristics and outcomes and whether this has an impact on the generalisability (external validity) of the study's findings.

### **3. Procedure to be examined**

#### **3.1 General description**

##### **Study part A: Epidemiological cohort study**

Epidemiological cohort study to examine determinants and predictors of long-term prognosis in patients with type 2 diabetes mellitus (1,500 patients) in GP care over a period of 20 years.

##### **Study part B: Randomised controlled trial**

As procedure to be examined, telephone counselling will be conducted as described in the following:

###### **I. Intervention group:**

- The intervention group will receive telephone counselling, which will be carried out by trained nurses of the participating GP practices.
- By using a patient-oriented questionnaire patients will be called in regular intervals (every 4 to 6 weeks, approx. 10 times) over a period of 12 months, and will be questioned and counselled regarding diabetes-related aspects.
- Each counselling session will take approx. 15 minutes.
- The usual diabetes therapy (as taken care of by the GP) will be continued independent of the telephone counselling.

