###### **II. Control groups (patients randomised to control group, and eligible patients unwilling to participate in the intervention study):**

- Patients in the control group will receive usual care, but will not receive telephone counselling sessions.

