### **Study part B**

In a sub-group of cohort study participants additionally: Open randomised controlled trial with about 124 patients each in intervention and control group. According to the „comprehensive cohort design“, patients who are eligible but do not agree to participate will be followed up as non-randomised control group (no telephone counselling; approx. 64 patients).

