### **Study part B**

In order to prevent a distortion of results by potential confounders, patients will be individually randomised. The randomisation will be conducted centrally in the study centre at the DKFZ for all eligible patients of the participating GP practices. The web-based patient randomisation service for multi-centre clinical trials of the Institute for Medical Informatics, Statistics and Documentation at the Medical University of Graz, Austria, will be used for the randomisation (<http://www.randomizer.at>). Because of the limited number of study participants and the number of participating GP practices, the minimisation method is used to ensure an equal distribution of potential influencing factors in the two randomised study arms. As influencing factors the GP practice (as study centre) and age and sex of the participants will be considered.

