## Study part B

Patients fulfilling the additional inclusion criterion for study part B will be either randomised into one of the two study arms of the trial or – if they do not consent to participate in the trial – will be assigned to the second control group. The intervention group will receive telephone counselling sessions every 4 to 6 weeks during the first 12 months after recruitment. The intervention and control groups will additionally receive standardised patient questionnaires (see above) after 6, 12 and 18 months. The diabetes therapy during the course of the intervention study, including occasioned diagnostic and therapeutic measures as well as incidence of potential diabetes-related complications (e.g. myocardial infarction) and hospital admissions, will be documented using the standardised follow-up GP questionnaires (see above) after the end of the intervention (at 12 and 18 months).

After completion of study part B the patients will be also followed-up in the context of the epidemiological cohort study.

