HbA1c will be determined at the beginning of the study as well as immediately and 6 months after the end of the intervention in all trial participants.

*Secondary outcomes:*

Diabetes mellitus is a chronic disease in which the further course of health (incidence of complications and sequelae) largely depends on a preferably integrated medical care as well as on lifestyle factors. Therefore the following secondary outcomes will be evaluated besides the primary outcome HbA1c:

- lipid metabolism control
- blood pressure
- body weight, physical activity, smoking
- health-related quality of life
- incidence of diabetes-related complications

- hospital admissions
- mortality.

The primary working hypothesis is that supportive telephone counselling in these patients helps improving the primary outcome of diabetes therapy (HbA1c). The secondary working hypothesis is that, as consequence, also secondary outcomes (diabetes-related complications, hospital admissions, mortality etc.) will improve.

The statistical examination includes the following analyses:

- a thorough description and comparison of control and intervention group regarding diabetes-related parameter (amongst others: age, sex, duration of diabetes, medication, body weight, comorbidity, life style factors),
- a thorough description and comparison of control and intervention group regarding the primary and secondary outcomes at the end of the intervention,
- analyses on the association of intervention and changes in outcomes during long-term follow-up (sustainability of the intervention),
- a thorough description and comparison of eligible patients unwilling to participate in the trial and of control and intervention group regarding the primary and secondary outcomes at the end of the intervention (assessment of external validity/generalisability of results).

The comparison of change in HbA1c in both study groups using multiple linear regression and adjusting for potential confounders will be the main analysis of the intervention study (study part B).

Further analyses will be conducted, also adjusting for potential confounders and using multivariate regression models (multiple linear regression or Cox proportional hazards models, depending on the outcome). These will be based on a priori formulated protocols for analyses. All analyses will be conducted using the statistical software SAS and under the supervision of the project leader.

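### GP-reported complications, and to a lesser degree hospital admissions, are at risk of differential ascertainment, because the practices that record them also question only the intervention arm by telephone until month 12

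*Protocol*

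**What the plan says.** Protocol section 3.1 (study part B, intervention group) provides "telephone counselling, which will be carried out by trained nurses of the participating GP practices". On the schedule it says "patients will be called in regular intervals (every 4 to 6 weeks, approx. 10 times) over a period of 12 months", and patients "will be questioned and counselled regarding diabetes-related aspects". For controls it says: "Patients in the control group will receive usual care, but will not receive telephone counselling sessions".

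Section 4 describes an "Open randomised controlled trial with about 124 patients each in intervention and control group". Under section 5, "patients will be individually randomised", so patients of both arms can belong to the same practice.

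Section 7 (study part A) has the attending GP complete the follow-up questionnaire for every patient. It covers incident diseases, especially diabetes complications, as well as specialist referrals and inpatient admissions. Section 7 (study part B) says that the course of therapy, complications and admissions "will be documented using the standardised follow-up GP questionnaires (see above) after the end of the intervention (at 12 and 18 months".

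Section 11 lists complications and admissions among the secondary outcomes. It compares the arms on the primary and secondary outcomes at the end of the intervention, and then plans "analyses on the association of intervention and changes in outcomes during long-term follow-up (sustainability of the intervention".

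**The concern.** The practice that delivers the intervention also reports the outcome. For one arm its nurses ask about diabetes-related matters every few weeks for a year; for the other arm they do not. A complication or admission mentioned in a call may reach the GP's record when the same event in a control patient would not. The Protocol describes no blinded event assessment, no required outside source, and no rule keeping call information off the outcome form.

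The extra contact ends at month 12, between the two readings on which sustainability is judged. If calls raise capture, the intervention arm would show relatively more events in months 0-12, which hides a benefit. Its recorded rate would then fall when the calls stop, which could pass for a late benefit. Complications and admissions are named in the objectives (section 2) and in the secondary working hypothesis (section 11), so those conclusions are at stake. Analysis cannot restore control-arm events that were never recorded.

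**Working it through.** **The Protocol's own figures.** Its only calculated result is the HbA1c power table in section 11 (n = 120 per group, SD 1.0, two-sided alpha 0.05). For a difference of 0.4: 0.4 / (1.0 × √(2/120)) = 3.098; 3.098 − 1.960 = 1.138; power = Φ(1.138) = 0.87, as stated. The other rows also reproduce. The call count is consistent: 52/6 = 8.7 to 52/4 = 13 calls a year, against about 10 stated. Neither figure bears on event capture.

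**Contact and recording by arm, from sections 3.1 and 7.**

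| | Intervention | Control |
|---|---|---|
| Practice calls, months 0-12 | about 10 | none |
| Practice calls, months 12-18 | none | none |
| GP outcome form | 12 and 18 months | 12 and 18 months |
| Patient questionnaires | 6, 12, 18 months | 6, 12, 18 months |
| HbA1c blood draw at the practice | baseline, 12, 18 months | baseline, 12, 18 months |

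Only the calls differ, and only until month 12.

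**Illustration of size.** The Protocol gives no event rates and no capture shares, so everything below is assumption. Let c1 be the share of true events recorded with calls and c0 the share without.

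- Apparent rate ratio in months 0-12 = true rate ratio × c1/c0.
- True rate ratio that would look like no effect = c0/c1. If capture fell fully back to c0 after month 12, this is also the factor by which the intervention arm's recorded rate would drop with no real change.

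| c1 vs c0 | Null appears as | True 0.80 appears as | c0/c1 |
|---|---|---|---|
| 95% vs 95% | 1.00 | 0.80 | 1.00 |
| 95% vs 90% | 0.95/0.90 = 1.06 | 0.80 × 0.95/0.90 = 0.84 | 0.90/0.95 = 0.95 |
| 95% vs 80% | 0.95/0.80 = 1.19 | 0.80 × 0.95/0.80 = 0.95 | 0.80/0.95 = 0.84 |

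**Effect on a significance test.** With 120 per arm, no true effect, and true risks of 5%, 10% and 20%, a two-sided two-proportion z-test at the 5% level rejects as follows:

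- 95% vs 90%: 5.1%, 5.2%, 5.5%.
- 95% vs 80%: 5.9%, 7.0%, 9.4%.

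False-positive inflation is modest. The larger risk in this range is that a real reduction is masked.

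**The case against.** A reader might infer that event capture does differ by arm, that the 12-month and sustainability comparisons are therefore biased by design, and that neither can be read as a treatment effect. The documents do not support this, for four reasons.

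- **The link is inferred.** Nothing in the Protocol says that call content reaches the GP form. Nurses make the calls; the GP completes one standardised form for all patients on the same schedule.
- **Controls are not out of sight.** Participants must be in diabetes care at the practice, and patients seen only in emergencies or exceptionally are excluded (section 6). Blood is drawn at the practice at 12 and 18 months in both arms, and the follow-up form includes physical findings (section 7). That gives a chance to catch up on missed events, which the simple capture model ignores.
- **The scope is limited.** The main analysis is change in HbA1c, measured by a central laboratory on one schedule. The sustainability analysis covers outcomes in general, including HbA1c and measured values that calls do not reach.
- **The capture shares have no source,** and in months 0-12 the direction is against the intervention.

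All four stand and narrow the point, but they do not remove it. A common form does not equalise what the person completing it knows. The statement in section 3.1 that usual therapy continues independently of counselling concerns treatment, not the flow of information. The patient questionnaires sent to both arms are a useful check, but section 7 assigns complications and admissions to the GP form. Who records events, and from what source, is study conduct fixed in sections 3 and 7, not a detail to be left to an analysis plan.

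**Conclusion.** The point holds as an unguarded risk, not as a demonstrated bias. It concerns GP-reported diabetes-related complications, chiefly the milder ones that come to light through questioning, checking or referral. Admissions are affected to a lesser degree. For major events that the GP would learn of anyway, the effect may be near zero.

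The size is unknown. The apparent rate ratio of 1.06 to 1.19 under no effect rests wholly on assumed capture of 95% vs 90% to 80%, with no catch-up at the 12-month visit; equal capture gives 1.00. The apparent later improvement further assumes that capture in the intervention arm returns to the control level once calls stop. The primary HbA1c comparison, mortality and measured values such as lipids, blood pressure and weight are not affected by this mechanism.

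**What to change.** **Section 7.** State that information known only from a counselling call is not a source for the GP outcome form. State that complications and admissions are taken from sources available alike in both arms: discharge letters, specialist reports and practice visits. Use the patient questionnaires already sent to both arms at 6, 12 and 18 months as a cross-check, not as the main source, since self-report in an open trial carries its own risk of differential reporting.

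**Section 11.** Report events identified through hospital care (admissions, myocardial infarction, death) separately from complications found by checking or referral. Show months 0-12 and 12-18 separately by arm. Say that a change after month 12 in the detection-sensitive complications will be interpreted with caution because contact changes at that point. A later effect should not be ruled out in advance, as a real lagged benefit is possible.

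**Cost.** This is protocol wording and an instruction to the practices; no new visit or instrument is needed. The downside is that a few real events known only from calls are not counted.

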###### **II. Control groups (patients randomised to control group, and eligible patients unwilling to participate in the intervention study):**

- Patients in the control group will receive usual care, but will not receive telephone counselling sessions.

#### **3.2 Effects (therapeutic, diagnostic)**

Objective of the study is to clarify whether and to what extent the concept of care in patients with type 2 diabetes mellitus with poor glycemic control can be improved.

#### **3.3 Unintended effects, other risks, strains for participants**

A blood sample will be collected from all participants at the beginning of the study, after 12 months (only from participants of the intervention study) and after 18 months. To further

minimise the low risk associated with the venous puncture, the blood collection will be conducted in the context of a venous puncture in GP routine care, if possible.

Unnecessary strains for the participating patients will be prevented by providing assistance for specific problems and giving participants the opportunity to withdraw their consent to participate at any time.

## **4. Study design**

### **Study part A**

Epidemiological cohort study in patients with type 2 diabetes mellitus

### **Study part B**

In a sub-group of cohort study participants additionally: Open randomised controlled trial with about 124 patients each in intervention and control group. According to the „comprehensive cohort design“, patients who are eligible but do not agree to participate will be followed up as non-randomised control group (no telephone counselling; approx. 64 patients).

## **5. Randomisation procedure**

### **Study part A**

Not applicable – observation study.

### **Study part B**

In order to prevent a distortion of results by potential confounders, patients will be individually randomised. The randomisation will be conducted centrally in the study centre at the DKFZ for all eligible patients of the participating GP practices. The web-based patient randomisation service for multi-centre clinical trials of the Institute for Medical Informatics, Statistics and Documentation at the Medical University of Graz, Austria, will be used for the randomisation (<http://www.randomizer.at>). Because of the limited number of study participants and the number of participating GP practices, the minimisation method is used to ensure an equal distribution of potential influencing factors in the two randomised study arms. As influencing factors the GP practice (as study centre) and age and sex of the participants will be considered.

## 6. Inclusion and exclusion criteria

### *Inclusion criteria:*

- Type 2 diabetes mellitus patients who are in diabetes care at one of the 10 collaborating GP practices in the Ludwigsburg area during the period of recruitment (presumably from 01.10.2008 – 31.12.2008),
- Ability and willingness to participate in the study.

For study part B additionally:

- $HbA_{1c} > 7,5\%$  (as being determined centrally at entrance to the cohort study for all participants).

### *Exclusion criteria:*

- Insufficient knowledge of the German language,
- Nursing home resident,
- Palliative care situation with limited life time,
- Patients seeing the GP for emergency care or by way of exception only.

## 7. Course of the study

### Study part A

During the recruitment period, all patients with type 2 diabetes mellitus of the participating practices will be informed about the planned study. Of diabetes patients giving consent to participate in the study (estimated number: N=1500) a blood sample will be drawn to determine  $HbA_{1c}$  in order to check for eligibility for study part B (inclusion criterion:  $HbA_{1c} > 7.5\%$ ).  $HbA_{1c}$  will be determined by a central external laboratory in the Ludwigsburg-area for all patients in order to guarantee the comparability of this essential study parameter. At this point, patients will receive the patient questionnaire by their GP, which they are asked to fill in at home and send to the Division Clinical Epidemiology and Aging Research at DKFZ. The  $HbA_{1c}$ -results will be passed on promptly to the Division Clinical Epidemiology and Aging Research at DKFZ by the external laboratory. The parts of the blood samples that are not needed for the determination of  $HbA_{1c}$  will be collected and frozen in the laboratory and then collectively sent to the Division Clinical Epidemiology and Aging Research at DKFZ for long-term storage and later analyses.

In order to investigate determinants and predictors of long-term prognosis in patients with type 2 diabetes mellitus, the following information relevant for the project will be collected by patients and their attending GPs at baseline as well as at all follow-up measurements (over a period of up to 20 years; first follow-up: after 18 months):

Standardised patient questionnaires:

Covering the following topics (amongst others):

- quality of life: e.g. SF12, EQ5D,
- sense of coherence: SOC13,
- patient assessment of chronic illness care (PACIC 5A, German version),
- diabetes-related disorders,
- blood glucose control,
- life style (including smoking, alcohol consumption, nutrition, physical activity),
- depression: e.g. German version of the Patient Health Questionnaires (PHQ9).

At baseline measurement, the following topics will be additionally covered:

- previous diabetes-related patient education;
- socio-demographic variables: education, marital status, occupation.

Standardised GP questionnaires:

• Recruitment questionnaire:

This questionnaire will be filled in by the attending GP for all patients at inclusion into the study. Especially the following topics will be documented:

- detailed disease history,
- diabetes: duration of disease, previous therapy, complications,
- comorbidity,
- medication at recruitment,
- laboratory results at recruitment,
- type of diabetes care: disease management program or usual care,
- appraisal of patient's compliance.

• Follow up-questionnaires:

The attending GP documents the following topics (among others) for all patients at all follow-up measurements:

- incident diseases (especially diabetes-complications),
- laboratory results (amongst others: fasting blood glucose, lipids, creatinine, albumin in urine),
- findings of physical examination (amongst others: body weight, blood pressure, pulse, sensory functions),
- medication,
- diabetes-related referrals to specialists (e.g. ophthalmologists, nephrologists),
- inpatient hospital admissions and their medical causes.

At the beginning of the study structural characteristics of the participating practices will be collected using a standardised questionnaire. These are in particular:

- type of practice: single or group practice, shared practice,
- year of establishment of the practice,
- additional qualifications,
- number of patients, share of private patients.

